### Standardization of perioperative care

The operations will be performed by two senior surgeons ([name] and [name]) who are equally skilled in T-tube drainage and Roux-en-Y HJ. Intraoperative flexible choledochoscopy (CHF-P20, external diameter, 4.9 mm; Olympus, Tokyo, Japan) will be routinely performed to explore the biliary ducts, identify the function of the SO and remove residual stones. All patients included in the study should successfully undergo cleaning of all ductal stones, removal of all strictures and elimination of the non-functioning liver segments that harbour bacteria and serve as foci of infection. For the patients with T-tubes, cholangiography will be performed to ensure that all the stones are clean before the T-tubes are removed. If there are residual stones, they could be cleaned through postoperative choledochoscopy. Indications for liver lobe resection will include a liver segment or lobe filled with stones that were inaccessible by other approaches for treatment, strictures associated with stones, atrophy of the affected liver segments or lobe, presence of liver abscess, or suspected cholangiocarcinoma. The selection criteria for hepatectomy will require patients to have Child’s A grade liver function and no evidence of portal hypertension. The grading criteria for SO function are as follows: normal—the shape of the SO is circular (Fig. 3a) or comma-like (Fig. 3b) with normal rhythmic contractions, a flexible choledochoscope cannot enter the duodenum and the SO can completely close without gaps during closure; SOL (shown in Additional file 3: Video S1-Grading criteria for the SO function laxity)—the shape of the SO is oval (Fig. 3c) or irregular (Fig. 3d), a flexible choledochoscope can enter the duodenum with some resistance, the SO cannot completely close during closure or reflux of food or methylene blue can be seen in the common bile duct during flexible choledochoscopy; and loss of function—the flexible choledochoscope can directly enter the duodenum, and no contractions are observed after the morphine-neostigmine test.

**Fig 3 Fig3:**
[figure not shown]
Shape of the sphincter of oddi. **a** Radial form. **b** Comma form. **c** Oval form. **d** Irregular form

**Additional file 3.** Grading criteria for the SO function laxity.

### Provisions for post-trial care

There is no anticipated harm and compensation for trial participation

### Data management and quality assurance

The principal investigators and data analysts will have access to the final cleaned dataset. All paper forms will be scanned and stored at the password cabinet in the First Affiliated Hospital of Anhui Medical University office of clinical trials. All electronic data will be coded and stored separately without the personal data in on a password-protected computer. The files of the participants will be stored for a minimum of 10 years after the end of the study. All relevant information for each subject should be recorded in the case report form (CRF) and inputted into the Microsoft Access database in a timely, truthful and precise manner by trained research staff. An explanation should be given for all missing data. Complete CRF pages will be checked by the principal investigator and the responsible monitor with respect to completeness and plausibility. The patients will also be informed of the outpatient follow-up interviews by telephone, and all items will be regularly accordingly assessed to the schedule shown in Fig. 2. Changes to the database can only be made with joint written consent from the data managers, statisticians and clinical research leaders. The results will be submitted for publication in peer-reviewed journals.

To ensure the safety and validity of the trial, the data will be overseen by an independent Data Safety Monitoring Board (DSMB) for efficacy outcomes and safety, which consists of surgical experts, statistics experts and ethics experts. It is independent from the sponsor and competing interests. During the trial, the DSMB is charged with providing advice recommendations that include (a) continuation of the study, (b) continuation with modification and (c) termination of the study.

### Confidentiality

All data will be treated as confidential. The data will be acquired only by researchers, research institutions and ethics committees who have signed a confidential disclosure agreement. The study will not release the individual identities of the participants without consent, except in special circumstances as required by law.

### Statistical analysis

The two-sided null hypothesis for the primary outcome measure states that both study interventions lead to a similar rate of stone recurrence; the alternative hypothesis is that one intervention will perform better than the other. The continuous variables will be recorded as the mean ± SD (for normally distributed variables) or medians and interquartile ranges (for skewed parameters) and will be statistically analysed with Student’s *t* test and the non-parametric Mann-Whitney *U* test, respectively.

Categorical data will be presented as frequencies and group percentages and compared with Fisher’s exact test. Graded data, including age, quality of life and Clavien-Dindo classification, will be compared with the Wilcoxon signed-rank test.

The odds ratio for having biliary complications will be determined with a logistic regression model. The homogeneity of the two groups will be described by comparing the demographic data and the baseline values.

All analyses will be performed on an intention-to-treat (ITT) basis. Statistical Package for the Social Sciences (SPSS) 10.0 (SPSS Inc., Chicago, IL, USA) will be used for statistical analysis. Statistical significance will be defined as *P* < 0.05.

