**Methods/design:**

In total, 210 patients who met the following eligibility criteria were included and were randomized to the choledochojejunostomy arm or T-tube drainage arm in a 1:1 ratio: (1) diagnosed with hepatolithiasis with SOL during surgery; (2) underwent foci removal, stone extraction and stricture correction during the operation; (3) provided written informed consent; (4) was willing to complete a 3-year follow-up; and (5) aged between 18 and 70 years. The primary efficacy endpoint of the trial will be the incidence of biliary complications (stone recurrence, biliary stricture, cholangitis) during the 3 years after surgery. The secondary outcomes will be the surgical, perioperative and long-term follow-up outcomes.

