### Number of patients needed

The sample size is based on a two-sided *t* test for differences with respect to the primary parameter and the primary analysis. In a retrospective analysis of our own series, the incidence of biliary complications was 30% in patients with HL with SOL undergoing T-tube drainage. The calculated sample size was 186 (93 per group), with 80% statistical power to detect a difference in the supposed incidence of biliary complications of 15% (30% in the T-tube drainage group versus 15% in the Roux-en-Y HJ group). Given an estimated withdrawal rate of 10%, the minimum required sample size would be 204 patients. We plan to enrol a total of 210 patients (105 per group).

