### Primary and secondary endpoints

All participants will be followed up regularly according to the schedule shown in Fig. 2 at the stated intervals after surgery for at least 3 years. At the follow-up visits, patients will undergo laboratory tests and abdominal ultrasonography as described in Fig. 2. CT or MRI will be performed in cases of suspected stone recurrence or cholangitis. Laboratory tests mainly include routine blood, liver and kidney function, electrolytes, procalcitonin, C-reaction protein, carcinoembryonic antigen, carbohydrate antigen 199 (CA199) and alpha-fetoprotein (AFP).

The primary efficacy endpoint of the trial will be the incidence of biliary complications (stone recurrence, biliary stricture, cholangitis). Stone recurrence will include any bile duct stones detected with any imaging modality during follow-up. Biliary stricture will be defined as clinically evident stenosis and subclinical stenosis proven by endoscopic examination or reoperation. The diagnosis of cholangitis will be based on clinical evidence (abdominal discomfort/pain, jaundice or fever associated with hepatolithiasis).

The secondary outcomes will be the surgical, perioperative and long-term follow-up outcomes. The surgical outcomes will include operative duration, intraoperative blood loss, intraoperative blood transfusions, stone distribution and SO function. The perioperative events occurring within 90 days after surgery will be recorded, including biliary leakage, wound infection, pulmonary infection, reoperation, hepatic injury, haemorrhage, bowel function recovery, intra-abdominal fluid collection or abscess, mortality, duration of postoperative hospital stay and total hospitalization expenditure. The indices of long-term follow-up outcomes will be hepatic injury, stone recurrence, biliary stricture, rate of unplanned readmission for HL, incidence of cholangitis and quality of life. Postoperative complications will be graded based on severity according to the Clavien-Dindo definition (shown in Additional file 2: Table S1) [8]. Long-term quality of life will be assessed by clinical grading according to Terblanche et al. [9]. Grades I and II constituted excellent or good results, grade III fair and grade IV poor (shown in Additional file 2: Table S2).

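### The null hypothesis for the primary outcome names stone recurrence alone, contradicting the composite primary endpoint on which the trial is defined and sized

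*Protocol article*

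**What the plan says.** The Statistical analysis section of the protocol article opens with the primary hypothesis. Its two-sided null, stated to be for the primary outcome measure, is that "both study interventions lead to a similar rate of stone recurrence". The alternative is that one of the two interventions does better.

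The other parts of the article describe a different primary outcome:

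- **Primary and secondary endpoints:** "The primary efficacy endpoint of the trial will be the incidence of biliary complications (stone recurrence, biliary stricture, cholangitis").
- **Abstract, Methods/design:** the same composite with its time window, "the incidence of biliary complications (stone recurrence, biliary stricture, cholangitis) during the 3 years after surgery".
- **Number of patients needed:** the control rate is for the composite ("the incidence of biliary complications was 30% in patients with HL with SOL undergoing T-tube drainage"), and so is the target difference, "30% in the T-tube drainage group versus 15% in the Roux-en-Y HJ group".
- **Discussion, in the Abstract and in the main text:** the aim is to find which drainage method better reduces biliary complications.
- **Secondary outcomes:** stone recurrence appears here in its own right, "The indices of long-term follow-up outcomes will be hepatic injury, stone recurrence, biliary stricture".

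Further down, the Statistical analysis section plans a logistic regression giving an odds ratio for biliary complications. It assigns Fisher's exact test to categorical data in general and sets significance at P < 0.05. It does not say which of these is the primary analysis.

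**The concern.** The sentence that states the primary hypothesis should point to the variable that decides the trial. Here it points to one component of the primary endpoint, which the article also lists as secondary. Three things are at stake.

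- **Choice of hypothesis.** Two hypotheses can each be presented as the prespecified primary one at P < 0.05. Unless the sentence is corrected before outcomes are known, a choice between them could be made after the results are seen.
- **Possible disagreement between the two.** Recurrence is any bile duct stone found on imaging, while cholangitis rests on clinical evidence, and surgeons and patients are not blinded. The composite and its stone component need not lead to the same conclusion.
- **Sample size.** The justification is written for the composite. A component cannot be more frequent than the composite that contains it, and no recurrence rate is given, so the stated size does not support a primary test of recurrence.

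**Working it through.** **The contradiction needs no arithmetic.** The null sentence says it concerns the primary outcome measure. The endpoint section and the Abstract define that measure as the three-part composite, and the sample size and aim follow that definition. The null sentence then names only the first part. No statement in the article reconciles the two.

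**Inputs for the illustration.** From the article: 30% versus 15% for the composite; 93 per group; a two-sided test; significance at P < 0.05. Assumed, because the article gives no recurrence rate: recurrence in the T-tube arm is a fraction *f* of the 30% composite rate, and hepaticojejunostomy halves it, as it is supposed to halve the composite.

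**The plan's own figure first.** The article states "The calculated sample size was 186 (93 per group), with 80% statistical power". With unpooled variance, n per group = (z for alpha + z for power)² × [p1(1−p1) + p2(1−p2)] / (p1−p2)².

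- Variance term: 0.30×0.70 + 0.15×0.85 = 0.3375. Divided by 0.15² = 0.0225, this is 15.
- Two-sided 5%: (1.960 + 0.842)² × 15 = 117.7, so 118 per group (121 with pooled variance).
- One-sided 5%: (1.645 + 0.842)² × 15 = 92.7, so 93 per group.

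The stated 93 is not reproduced two-sided. It is reproduced with one-sided 5%. That is a separate sample-size matter, noted here only because it explains why the composite row below is not 80%.

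**Power at 93 per group, two-sided 5%.** Power = Φ(|p1−p2| / SE − 1.960), with SE = √{[p1(1−p1) + p2(1−p2)] / 93}.

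| Outcome tested | Rates | SE | Difference / SE | Power |
|---|---|---|---|---|
| Composite | 30% v 15% | √(0.3375/93) = 0.0602 | 2.490 | Φ(0.530) ≈ 70% |
| Recurrence, *f* = 0.80 | 24% v 12% | √(0.2880/93) = 0.0556 | 2.156 | Φ(0.196) ≈ 58% |
| Recurrence, *f* = 0.67 | 20% v 10% | √(0.2500/93) = 0.0518 | 1.929 | Φ(−0.031) ≈ 49% |
| Recurrence, *f* = 0.50 | 15% v 7.5% | √(0.1969/93) = 0.0460 | 1.630 | Φ(−0.330) ≈ 37% |

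With pooled variance the first, third and fourth rows are 69%, 48% and 37%. At the full 105 per group, also pooled, they are 74%, 53% and 40%.

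**The case against.** The strongest reply is that this is a drafting slip and the intended reading is clear. The null sentence refers to the primary outcome measure, which the article defines elsewhere as the composite. The only endpoint-specific analysis in the section is the logistic regression for biliary complications. A later switch to recurrence as primary would contradict the published endpoint definition. Much of this stands: the two hypotheses are not equally supported, and the composite is the dominant reading. It does not remove the contradiction, because the regression is not labelled primary, whereas the recurrence null is tied explicitly to the primary outcome.

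Three stronger readings are tempting, and the article does not support them.

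- **That the confirmatory test is on the wrong variable.** The null sentence names no test, and the same section models the composite.
- **That testing recurrence would hide effects running in opposite directions.** The main Discussion cites retrospective evidence that hepaticojejunostomy reduces both cholangitis and recurrence in patients with sphincter dysfunction. No part of the article compares stricture rates between the arms.
- **That the trial's power is really 37% to 58%.** Those figures rest on assumed recurrence shares and an assumed halving. Cholangitis is defined through symptoms linked to hepatolithiasis, so its overlap with recurrence may be large. The share would then be high and the loss smaller.

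**Conclusion.** The point holds as an internal contradiction. The primary null hypothesis is stated for stone recurrence, while the endpoint definition, sample size and aim are for the composite, and recurrence is listed as secondary. As written, the section leaves two candidate primary hypotheses and ranks neither. The article does state the primary hypothesis and states it inconsistently, so this is not a detail left to a fuller protocol or an SAP.

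The contradiction itself rests on no assumption. Its cost in power cannot be computed from the article. Under a halving of recurrence and shares of 80%, 67% or 50%, a recurrence-only test at 93 per group would lose roughly 12, 21 or 33 percentage points against the composite's 70%. The gap between that 70% and the stated 80% does not come from this contradiction, and correcting the null would not close it.

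**What to change.** Replace the null-hypothesis sentence with one to this effect: the proportion of patients with at least one biliary complication (stone recurrence, biliary stricture or cholangitis) within 3 years of surgery is equal in the two arms, against a two-sided alternative. Add that this comparison is the single primary analysis, and say which of the methods already listed supplies its P value. Keep stone recurrence as a secondary outcome. Any SAP should carry the same wording.

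The cost is a sentence or two, made before outcome data are examined. It changes no sample-size input, eligibility criterion, data collection or patient care.

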**Discussion:**

This is a prospective, single-centre and randomized controlled two-group parallel trial designed to demonstrate which drainage method (Roux-en-Y hepaticojejunostomy or T-tube drainage) can better reduce biliary complications (stone recurrence, biliary stricture, cholangitis) in hepatolithiasis patients with SOL.

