### Randomization and blinding

To achieve comparable groups of known and unknown risk factors, randomization will be performed. Patients meeting the eligibility criteria will be randomly assigned (1:1) to the T-tube drainage arm or Roux-en-Y HJ arm by computer-generated allocation based on the envelope method and the hierarchical block randomization method. The envelopes will be opened after common bile duct exploration.

Blinding of the surgeons and patients is not feasible due to the obviously different characteristics of the two types of biliary drainage. However, the statisticians will be blinded to the treatment allocation during data collection and analysis.

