There is no consensus on which drainage method is better for HL patients with SOL, and there are no prospective randomized controlled studies that have evaluated the effects of different drainage methods. The biliary drainage method is chosen arbitrarily and is mostly based on the surgeon’s habits. When performing bile duct exploration during surgery, most surgeons often judge the function of the sphincter with a manometry probe or catheter and determine which biliary drainage method is needed. These methods are mostly empirical, lack scientific evaluation and cannot accurately reflect the true function of the SO. This study design features methods and evaluation criteria to evaluate the SO function during the operation. In this prospective randomized controlled study, the patients will be divided into the HJ group and the T-tube drainage group. The postoperative follow-up is standardized. Through statistical analysis of the results of the two groups, a systematic evaluation can be performed to recommend the best surgical method for HL patients with SOL. We believe that the results of this trial will significantly contribute to the evidence on which biliary drainage method is better for HL patients with SOL.

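### The plan names the Wilcoxon signed-rank test, a paired test, for age, quality of life and Clavien-Dindo grade, although the two arms are independent

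*Protocol article*

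**What the plan says.** The Statistical analysis section sorts variables into three classes, each with its own test.

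- Continuous variables are summarised by mean and SD or by median and interquartile range. They "will be statistically analysed with Student’s *t* test and the non-parametric Mann-Whitney *U* test, respectively".
- Categorical data go to Fisher's exact test.
- For the third class: "Graded data, including age, quality of life and Clavien-Dindo classification, will be compared with the Wilcoxon signed-rank test".

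The design is given in the Discussion part of the abstract: "This is a prospective, single-centre and randomized controlled two-group parallel trial". The Randomization and blinding section has patients "randomly assigned (1:1) to the T-tube drainage arm or Roux-en-Y HJ arm by computer-generated allocation". The main Discussion states the purpose as a comparison of the arms: "Through statistical analysis of the results of the two groups".

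Under Primary and secondary endpoints, quality of life is a four-level long-term grade: "Grades I and II constituted excellent or good results, grade III fair and grade IV poor". Clavien-Dindo grade describes the severity of postoperative complications.

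**The concern.** The signed-rank test ranks within-pair differences, so it needs a partner for every observation. In a parallel-group trial with individual allocation there is none. Taken literally, the sentence gives the analyst two options. Either the software refuses because the arms have different lengths, or it pairs the first T-tube record with the first hepaticojejunostomy record, the second with the second, and so on. The second option gives a P value that depends on file order, which carries no information about treatment.

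Complication severity and long-term quality of life belong to the trial's stated aim of assessing safety and long-term outcome. Their prespecified test should be one that can be run and that returns one answer. A silent switch to another test at analysis would be an undocumented departure from the published plan.

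Age is a smaller matter. It is listed as graded data, yet it would ordinarily fall under the rule for continuous variables in the same section.

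**Working it through.** **1. Is there any pairing that would justify the test?** The article gives no figure to reproduce here, so the first step is to set the texts side by side.

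- Between patients: allocation is individual and 1:1, and no matching is described. Blocked allocation does not create pairs.
- Within patients: age is a single baseline value. Clavien-Dindo grade exists only after surgery. Quality of life is a long-term grade, and no before-after contrast is described for it.
- Same section: skewed continuous variables get the Mann-Whitney U test, which is for independent samples. The same two arms are thus treated as independent for one class of variable and as paired for another.

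No pairing exists for any of the three named variables.

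**2. Will the arms be equal in size?** The sample-size section plans 105 per arm and allows for 10% withdrawal, and the Withdrawal section says the information of withdrawn patients will not be used. Assume each patient withdraws independently with probability 0.10. The number remaining per arm then has variance 105 × 0.9 × 0.1 = 9.45. The chance that two such arms end exactly equal is about 1 / (2 × √(π × 9.45)) = 0.09. Unequal arms are therefore likely for long-term quality of life, and less certain for early complication grade or age. With 93 against 90 observations, the software returned an error.

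**3. If the arms are equal, what does the P value depend on?** The article gives no grade distribution, so the following counts are an assumption: 93 per arm, grades I to IV of 42/23/19/9 (arm A) and 56/21/11/5 (arm B).

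Rank-sum test:

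- Pooled counts: 98, 44, 30, 14 (N = 186). Midranks: 49.5, 120.5, 157.5, 179.5.
- Rank sum of arm A: 42 × 49.5 + 23 × 120.5 + 19 × 157.5 + 9 × 179.5 = 9458.5.
- Expected: 93 × 187 / 2 = 8695.5. Difference: 763.
- Tie term: Σ(t³ − t) / [N(N − 1)] = 1,055,934 / 34,410 = 30.69.
- Variance: (93 × 93 / 12) × (187 − 30.69) = 112,663; SD = 335.7.
- z with continuity correction: (763 − 0.5) / 335.7 = 2.27, two-sided **P = 0.023**, whatever the row order.

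Signed-rank test on the same counts, with arm B randomly re-ordered against arm A 5,000 times (four runs with different random seeds):

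| Quantity | Result |
|---|---|
| Smallest P | 0.002 to 0.004 |
| Central 95% of P values | about 0.011 to 0.046 |
| Largest P | 0.07 to 0.09 |
| Share below 0.05 | about 99% |

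The same patients with the same grades can give P values on either side of 0.05, although in this example few pairings cross it.

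**4. Is the error rate inflated?** Simulated over 2,000 trials with 93 per arm and random pairing, assuming grade probabilities of 0.45/0.25/0.20/0.10 in both arms under no difference and 0.58/0.23/0.13/0.06 in one arm under a difference:

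| | Signed-rank | Mann-Whitney |
|---|---|---|
| Type I error | 0.048 | 0.050 |
| Power | 0.485 | 0.497 |

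The two tests disagreed on significance in 8.3% of trials when a difference existed. Average behaviour is close; the result in any single trial is arbitrary.

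**The case against.** The strongest reply is that this is a slip of the pen. The section already names the right independent-samples rank test for skewed data, so signed-rank was probably written for rank-sum. On that reading the intended analysis is sound and one term is wrong. This is plausible, but it is an inference: nothing in the article corrects the wording, so the text still has to be changed.

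A second reply is that the reach is small. This stands. The primary endpoint is binary and falls under Fisher's exact test and logistic regression. The article does not rank its secondary outcomes, so the two grades cannot be called the main ones. Age carries no treatment conclusion, and it may be meant as age bands, which the article leaves open. A rank-sum test would be valid either way.

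A third concerns the numbers. The grade distributions are assumed, and the extremes of many re-pairings show dependence on order; they do not estimate harm in this trial. That also stands.

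A reader might go further and infer that the test would produce a flood of false positives. A rate of about 82–83% can be produced for a continuous variable if each arm is first sorted by the variable under test and then matched rank to rank. Nothing in the article describes or implies such handling, and it would break up the patient-level records.

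**Conclusion.** The point holds as an error in the named test. A paired test is prescribed for three variables in a design with no pairs. It cannot be run with unequal arms, and with equal arms its P value depends on row order. In the illustration the P value ranged from about 0.002–0.004 to 0.07–0.09, against a single rank-sum value of 0.023.

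It does not hold as a claim of inflated type I error, which stays near 5% under random pairing, or as a threat to the primary analysis or the sample size. Two secondary measures and one baseline descriptor are affected, so this is something that should be fixed and does not rank as a critical defect.

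That the test does not fit rests on the article's text alone. The sizes rest on assumed grade distributions, 93 analysed per arm and, for the chance of unequal arms, independent withdrawal at 10%.

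**What to change.** In the Statistical analysis section, replace the signed-rank test with the Wilcoxon rank-sum (Mann-Whitney U) test, corrected for ties, for quality of life and Clavien-Dindo grade. Take age out of the graded data and analyse it under the rule for continuous variables in the same section. If age is recorded in bands, say so and use the rank-sum test.

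Proportional-odds regression, giving an odds ratio with a confidence interval, would be a useful addition for the two grades, but it is optional.

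The cost is one line of wording, entered as a dated change before the analysis. Design, sample size, data collection and conduct are unchanged.

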**Fig 2 Fig2:**
[figure not shown]
Schedule of enrollments, interventions and assessments. Abbreviations: t_1_, 3 months after surgery; t_2_, 6 months after surgery; t_3_, 1 year after surgery; t_4_, 2 years after surgery; t_5_, 3 years after surgery

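### The 3-year primary endpoint is analysed only by yes/no methods, while the withdrawal rule conflicts with intention to treat and the 3-year limit is not repeated in the endpoint section

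*Protocol article*

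**What the plan says.** - **Endpoint.** The abstract (Methods/design) gives the primary endpoint as "the incidence of biliary complications (stone recurrence, biliary stricture, cholangitis) during the 3 years after surgery". The section Primary and secondary endpoints names the same composite without the 3-year limit. It follows patients "at the stated intervals after surgery for at least 3 years" and counts any bile duct stone that imaging finds in follow-up.
- **Visits.** The Fig. 2 legend lists "3 months after surgery; t_2_, 6 months after surgery; t_3_, 1 year after surgery; t_4_, 2 years after surgery; t_5_, 3 years after surgery".
- **Sample size.** Number of patients needed assumes "30% in the T-tube drainage group versus 15% in the Roux-en-Y HJ group" and then allows for loss ("Given an estimated withdrawal rate of 10" per cent), with 105 per group planned.
- **Analysis.** The section Statistical analysis says "The odds ratio for having biliary complications will be determined with a logistic regression model". It gives Fisher's exact test for categorical data and puts every analysis on an intention-to-treat basis. It names no method that uses time at risk.
- **Withdrawal.** The Withdrawal section says that the information of a patient who withdraws is not used in the study. Its next sentence allows the team to go on recording that patient's outcome data.

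**The concern.** These statements do not fit together. A patient who leaves event-free at month 18 has no 3-year status. A yes/no analysis has to drop that patient, count the patient as event-free, or impute. The Withdrawal section points to dropping, and read literally it also removes patients who had a complication before they withdrew. That is not intention to treat.

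At stake are some power and, more importantly, an open choice in the primary analysis. Neither patients nor surgeons are blinded and the two operations differ greatly, so unequal withdrawal between arms is plausible. If it occurs, the result depends on a handling rule that the protocol states in two incompatible ways. Separately, an endpoint section with no upper limit on follow-up leaves room to count events after 3 years, and a plain logistic model has no term for unequal time at risk.

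**Working it through.** **Inputs from the protocol:** 30% v 15%, 80% power, two-sided test, P < 0.05, 186 patients before withdrawal, 10% withdrawal, 105 per arm enrolled.

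**1. The plan's own figure.** With a t test on a binary outcome, n per arm = (z_α + z_β)² × (0.30×0.70 + 0.15×0.85) / 0.15² = (z_α + z_β)² × 15.
- Two-sided: (1.960 + 0.842)² × 15 = 117.7, so 118 per arm.
- One-sided: (1.645 + 0.842)² × 15 = 92.7, so 93 per arm.

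The stated 93 per arm matches only a one-sided test. That is a separate point. Here it sets the baseline: two-sided power for two proportions is 74.3% at 105 per arm with no withdrawal.

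**2. Equal 10% withdrawal, observed rates.** Assume exponential event and withdrawal times and non-informative withdrawal. With L = −ln(1−p) and M = −ln(1−d), the chance of an event seen before withdrawal and within 3 years is L/(L+M) × [1 − (1−p)(1−d)].
- T-tube: 0.3567/0.4620 × (1 − 0.63) = 28.6%.
- HJ: 0.1625/0.2679 × (1 − 0.765) = 14.3%.

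These are the observed rates if withdrawn patients count as event-free. Excluding only event-free withdrawals gives 0.2856/(0.2856 + 0.63) = 31.2% and 0.1426/(0.1426 + 0.765) = 15.7%. Excluding all withdrawn patients leaves 30% and 15%, on about 210 × 0.9 = 189 patients. The formula for two proportions then gives 69.8% power at 94.5 per arm.

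**3. Simulated power.** 10,000 trials per row, 105 per arm, 30% v 15%, two-sided 5%, Wald test of an unadjusted logistic model against log-rank. Monte Carlo standard error is about √(0.7×0.3/10,000) = 0.5 points.

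| Withdrawal, T-tube / HJ | Log-rank | Yes/no: event-free withdrawals excluded | Yes/no: withdrawn counted event-free | Yes/no: all withdrawn excluded |
|---|---|---|---|---|
| 0 / 0 | 74.7% | 74.0% | 74.0% | 74.0% |
| 10% / 10% | 72.4% | 71.4% | 71.1% | 69.4% |
| 20% / 20% | 69.9% | 68.5% | 68.6% | 63.8% |
| 5% / 15% | 73.1% | 65.9% | 78.0% | 69.6% |
| 15% / 5% | 72.5% | 77.4% | 64.5% | 70.1% |

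Under no effect (30% in both arms), all methods reject in 5.1% to 5.3% of trials with equal 10% withdrawal, and in 4.5% to 5.9% with 5%/15% or 15%/5%.

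**4. Apparent difference under unequal withdrawal (true value 15.0 points), same formula.**
- 5%/15%: event-free withdrawals excluded, 30.6% − 16.1% = 14.5 points. Counted event-free, 29.3% − 13.9% = 15.4 points.
- 15%/5%: excluded, 31.9% − 15.3% = 16.5 points (before rounding of the rates). Counted event-free, 27.8% − 14.6% = 13.2 points.

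The shift is below 2 points either way, yet power moves by about 12 to 13 points between the two rules.

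**The case against.** The endpoint in the abstract is a fixed-window incidence and the trial is sized on two proportions. A yes/no comparison at 3 years fits both, so the model is legitimate. Logistic regression can be combined with multiple imputation, and the rule for missing outcomes may sit in an analysis plan that is not shown. All of this stands.

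The discarding is written in the Withdrawal section and does not come from the logistic model. Under that rule a log-rank test would lose the same patients. This also stands, and it is why changing the model alone repairs nothing.

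Three stronger readings are tempting but not supported:

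- **That withdrawn patients will be counted as event-free.** The protocol says this nowhere. That column of the table shows only what such a choice would do.
- **That early enrollees will be counted over nearly 7 years.** With no limit, and observation from February 2020 to December 2026, constant hazards would give 1 − 0.7^(6.9/3) = 56% risk under T-tube. But the abstract fixes 3 years and the listed visits end there. What remains is an endpoint section that omits the limit.
- **That withdrawal will be strongly unequal.** The protocol gives one overall figure of 10%. The unequal rows are assumptions used to show sensitivity.

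A time-to-event analysis has limits as well. Silent stones are dated only to the interval between visits, which is a year long after month 12. Informative withdrawal would bias it too, and death, which the protocol lists as an outcome, needs handling as a competing event.

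**Conclusion.** The concern holds in limited form. What the document fixes badly is the combination: a 3-year incidence, 10% expected withdrawal, only yes/no methods, a withdrawal rule at odds with intention to treat, and an endpoint section without the 3-year limit. Choosing logistic regression is not in itself a mistake.

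At equal 10% withdrawal the cost is about 1 to 3 points of power, with type I error near 5%. The stronger reason to act is stability. With 5% v 15% withdrawal in either direction, yes/no power spans 64.5% to 78.0% according to handling, against 72.5% to 73.1% for log-rank. These figures assume constant hazards, exponential and non-informative withdrawal, exactly known event times and the protocol's own rates. The change is worth making because it is cheap and asks the same 3-year question of data already scheduled for collection. The gain in power alone would be a weak reason.

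**What to change.** 1. In Primary and secondary endpoints, state that the primary endpoint counts events up to 3 years after surgery.
2. Reconcile the Withdrawal section with intention to treat, so that data up to withdrawal, and any outcome data still recorded with consent, are analysed. Without this step the next one has no effect.
3. Analyse time to first biliary complication up to 3 years: Kaplan-Meier 3-year incidence per arm, the difference with its 95% CI, and a log-rank test. Censor at the last assessment and treat death before a complication as a competing event (a cumulative incidence estimate in place of Kaplan-Meier if deaths occur). Keep the logistic odds ratio as supportive. At minimum, prespecify this as a sensitivity analysis to the yes/no comparison and state there how patients without a 3-year status enter it.

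**Cost.** Protocol wording and modest programming, with no new visits or data. If the log-rank test becomes primary, the sample size text should be restated to match. The drawbacks are a modest power gain, silent stones dated only to the visit interval, and no protection against informative withdrawal.
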